**NL54380.042.15 FACET study**

Table 1: Visit plan FACET study

|  | Visit plan |  |  |  |  |  |  | | | |
| --- | --- | --- | --- | --- | --- | --- | --- | --- | --- | --- |
|  |  | **Visit 1** Baseline (preoperative) | **Visit 2**  Procedure | **Visit 3**  Discharge | **Visit 3.1**  **t/m 3.5**  week 1-5 after OK | **Visit 4**  6 weeks after OK | **Visit 5**  26 weeks after OK | **Visit 6**  52 weeks after OK | **Visit 7**  78 weeks after OK | **Visit 8**  104 weeks after OK |
| 1 | Informed consent | x |  |  |  |  |  |  |  |  |
| 2 | Function X-ray | x |  |  |  |  |  |  |  |  |
| 3 | MRI and/or CT | x |  |  |  |  |  |  |  |  |
| 4 | Preoperative history | x |  |  |  |  |  |  |  |  |
| 5 | Clinical evaluation | x |  | x |  | x |  |  |  |  |
| 6 | Randomization | x |  |  |  |  |  |  |  |  |
| 7 | Operative detail |  | x |  |  |  |  |  |  |  |
| 8 | Patient self- assessment* | x |  |  | X (VAS arm and neck pain) | x | x | x | x | x |
| 9 | (S)AE recording and reporting |  | x | x |  | x | x | x | x | x |
| 10 | Costs | x |  | x |  | x | x | x | x | x |

*Patient self-assessment questionnaires will be web based and assessed at baseline, 6, 26, 52,78 and 104 weeks after surgical procedure

Evaluations during the study

- 1. Signing informed consent.

Prior to the start of the study a signed and dated informed consent will be obtained from the patient.

- 1. Function X ray

An X-ray of the neck and arm will be performed and is standard care.

- 1. MRI and/or CT scan

An MRI and/or CT scan will be performed to assess inclusion and exclusion criteria. These scans are part of normally care for these patients. If one of these tests is made 6 months or less before the surgical procedure, the information can be used an no new scan has to be made.

- 1. Preoperative history

From standard care procedures preoperative history is obtained including length, weight, ASA score, number of months/years of neck and arm pain, diagnosis, number of months the patient is diagnosed for cervical soft/osteophytic disc disease, signs and symptoms, other significant illnesses, pain medication, smoking history, use of NSAIDs. Medical charts will be used to verify this information.

- 1. Clinical evaluation

At baseline, discharge and 6 weeks follow up, information on signs and symptoms, reflexes and strength, will be assessed which is according to the standard care.

- 1. Randomization

If a patient is eligible and after informed consent completion the patient will be randomized to undergo one of the two procedures (FOR or ACDF).

- 1. Operative detail

During the operation information about the operative procedure will be obtained from the medical record of the patient such as date and type of procedure, which level is operated, use of implants, and the appearance of complications.

- 1. Patient self-assessment

The self-reported brachialgia (VAS), ODOMs criteria, Work Ability Index (WAI), quality of life (EQ-5D), neck pain (VAS), Neck Disability Index (NDI), Productivity Costs (iPCQ) and Medical Consumption (iMCQ) will be assessed by using web based questionnaires. Filling out these questionnaires takes about 30 minutes per follow up time and is additional information due to the study.

- 1. (S)AE reporting

Throughout the study (S)AE’s have to be recorded and reported according to the protocol.

- 1. Costs

Cost data will be collected in an electronic CRF and by questionnaires. Included costs will be those of the surgical procedure (either FOR or ACDF), hospital care (including costs for treating complications), medication related to the diagnosis, outpatient visits, GP visits, home care, and productivity costs due to absence from work. (Productivity Costs Questionnaire iPCQ, Medical Consumption Questionnaire iMCQ) . Unit prices will be determined according to Dutch guidelines (6).

In total 308 patients will be included in 6 centres in the Netherlands. In table 2 the enrolment schedule of the participating centres is showed.

Table 2: Patient enrolment schedule participating Centres.

| Patient enrolment schedule participating Centres | | | | | | | | | | | | | |
| --- | --- | --- | --- | --- | --- | --- | --- | --- | --- | --- | --- | --- | --- |
|  | Dec 2015 | Jan 2016 | Feb 2016 | March 2016 | April 2016 | May 2016 | June 2016 | July 2016 | Aug 2016 | Sept 2016 | Oct 2016 | Nov 2016 | Total  enrolment 1 yr |
|  |  |  |  |  |  |  |  |  |  |  |  |  |  |
| UMCG | 3 | 3 | 3 | 3 | 3 | 3 | 3 | 3 | 2 | 2 | 3 | 3 | 34 |
| Martini  ziekenhuis | 2 | 2 | 2 | 2 | 2 | 2 | 2 | 2 | 2 | 2 | 2 | 2 | 24 |
| Radboud UMC | 2 | 2 | 2 | 2 | 2 | 2 | 2 | 2 | 2 | 1 | 2 | 2 | 23 |
| Atrium/Orbis ziekenhuis | 2 | 2 | 2 | 2 | 2 | 2 | 2 | 2 | 1 | 1 | 2 | 2 | 22 |
| MS Twente | 2 | 2 | 2 | 2 | 2 | 2 | 2 | 2 | 2 | 3 | 3 | 3 | 27 |
| MC  Haaglanden | 2 | 2 | 2 | 2 | 2 | 2 | 2 | 2 | 2 | 2 | 2 | 2 | 24 |
|  | | | | | | | | | | | | | 154 |
|  | Dec 2016 | Jan 2017 | Feb 2017 | March 2017 | April 2017 | May 2017 | June 2017 | July 2017 | Aug 2017 | Sept 2017 | Oct 2017 | Nov 2017 | Total  enrolment 2 yr |
| UMCG | 3 | 3 | 3 | 3 | 3 | 3 | 3 | 3 | 2 | 2 | 3 | 3 | 34 |
| Martini ziekenhuis | 2 | 2 | 2 | 2 | 2 | 2 | 2 | 2 | 2 | 2 | 2 | 2 | 24 |
| Radboud UMC | 2 | 2 | 2 | 2 | 2 | 2 | 2 | 2 | 2 | 1 | 2 | 2 | 23 |
| Atrium/Orbis  ziekenhuis | 2 | 2 | 2 | 2 | 2 | 2 | 2 | 2 | 1 | 1 | 2 | 2 | 22 |
| MS Twente | 2 | 2 | 2 | 2 | 2 | 2 | 2 | 2 | 2 | 3 | 3 | 3 | 27 |
| MC  Haaglanden | 2 | 2 | 2 | 2 | 2 | 2 | 2 | 2 | 2 | 2 | 2 | 2 | 24 |
|  | | | | | | | | | | | | | 154 |
|  | | | | | | | | | | | | Total | 308 |

- 1. **Withdrawal of individual subjects**

Subjects can leave the study at any time for any reason if they wish to do so without any consequences. The investigator can decide to withdraw a subject from the study for urgent medical reasons.

- - 1. **Replacement of individual subjects after withdrawal**

The goal is to reach 308 patients. When a patient withdraws from the study, he/she will not be replaced since 10% loss of inclusion is calculated within the power calculations of the trial.

- - 1. **Follow-up of subjects withdrawn from treatment**

There will be no follow up of patients who are withdrawn from the study before the surgical procedure has taken place. If patients are withdrawn after they have received the treatment there will be follow up of medical data when necessary without bothering and with permission of the patient. Data of patients after withdrawal will be used and analysed with the intention to treat principle.

- - 1. **Premature termination of the study**

Premature suspension of the study will only occur in specific situations:

- Inclusion ratio: if inclusion one year after the last Centre has included its first patient is in total more than 50% below the amount of patients intended to include in all 6 centres, the study will be terminated.
- Patient health: there are no adverse reactions known on which termination of this study will be mandatory. Both surgical procedures are standard care.

The Medical Ethics committee will be informed about the suspension.

1. **SAFETY REPORTING**
   1. **Section 10 WMO event**

In accordance to section 10, subsection 1, of the WMO, the investigator will inform the subjects and the reviewing accredited METC if anything occurs, on the basis of which it appears that the disadvantages of participation may be significantly greater than was foreseen in the research proposal. The study will be suspended pending further review by the accredited METC, except insofar as suspension would jeopardise the subjects’ health. The investigator will take care that all subjects are kept informed.

- 1. **AEs, SAEs and SUSARs**
     1. **Adverse events (AEs)**

Adverse events are defined as any undesirable experience occurring to a subject during the study, whether or not considered related to intervention. The following complications are known by the researchers and are described in the literature. These complications will be listed as adverse events. No other adverse events will be administrated. The complications that will be assessed are the following:

- Death
- Thrombosis
- Pulmonary embolism
- Urinary retention
- Post-operative bleeding / Hematoma
- Post-operative wound infection
- Nerve root injury
- Dural tear
- Post-operative cerebrospinal fluid leakage
- Implant malposition
- Vascular injury
- Blood loss
- Urinary infection
- Spinal cord injury
- Esophagus injury
- Hoarseness
- Pneumonia
- other

Complications will be written down in the eCRF as adverse events.

- - 1. **Serious adverse events (SAEs)**

A serious adverse event is any untoward medical occurrence or effect that at any dose:

- results in death;
- is life threatening (at the time of the event);
- requires hospitalisation or prolongation of existing inpatients’ hospitalisation;
- results in persistent or significant disability or incapacity;
- is a congenital anomaly or birth defect;
- Any other important medical event that may not result in death, be life threatening, or require hospitalization, may be considered a serious adverse experience when, based upon appropriate medical judgement, the event may jeopardize the subject or may require an intervention to prevent one of the outcomes listed above.

Reporting procedure applies to all SAE's occurring from the time a subject gives consent until the end of the study. A life threatening SAE, or SAE with death as a result, must be reported within 7 days after the local investigator has been informed. Other SAEs must be reported within 15 days. The study coordinator is responsible for reporting SAEs at CCMO module ‘ToetsingOnline’.

For individual sites, the primary investigator completes the SAE report providing as much

detailed information as known and relevant to the event. The primary investigator sends the complete SAE form by e-mail to the UMCG study coordinator within 24 hours of discovery of the event.

Thus, the coordinating investigator will be notified by email or telephone within 24 hours after discovery of the event. Using the CCMO module ‘ToetsingOnline’, all SAEs will be reported to the

CCMO and central METC. The reporting will occur within 15 days after the investigator has first received information on the SAE. For fatal or life-threatening cases a preliminary report will be offered within 7 days followed by a complete report within 8 days.

The following SAE’s do not require immediate reporting but will be reported once yearly in line listings to the accredited METC that approved the protocol:

- Elective hospitalization for pre-existing conditions that have not been exacerbated by trial treatment
- A hospitalization which was planned before the subject consented for study participation and where admission did not take longer than anticipated
  - 1. **Follow-up of adverse events**

All AEs will be followed until they have abated, or until a stable situation has been reached. Depending on the event, follow up may require additional tests or medical procedures as indicated, and/or referral to the general physician or a medical specialist.

- 1. **Safety Committee**

Because of the low to moderate risk for participants in the study a Data Safety Monitoring Board is not needed. To ascertain that the study is safe for participants, the study coordinator will report monthly a list of all (S)AE’s to the Principle Investigator (PI). In case the PI ascertain that more (S)AE’s occur in one of the two arms compared to the other arm, he will ask three independent physicians to form a safety committee and judge the safety of the subjects of the study. Detailed information on the trial and the (S)AE’s will be provided to the safety committee.

1. **STATISTICAL ANALYSIS**
   1. **Primary study parameter(s)**

Due to the requirements of ZONMW the analyses will be done at 78 weeks, however end of trial analyses will be done at 104 weeks and these data will be published. The primary endpoint (Odom's criteria and self-reported brachialgia) will be analysed as appropriate depending on data distribution with a one sided

0.05 level of significance (non-inferiority). Detailed descriptive statistics will be provided for the data collected and 95% confidence intervals will be calculated for all relevant estimates. Clinical follow-up data will be analysed by analysis of covariance (ANCOVA) or generalized model alternatives for categorical or semi quantitative data. Changes within the treatment groups over time as well as differences between groups will be assessed by intention-to-treat analyses. Also the primary analysis will follow the per protocol principle. Sensitivity analysis will be provided to evaluate robustness of the results with regard to unexpected circumstances (for example, impact of ‘cross-over’ patients who are not treated as randomized but are required to be analysed as randomized and centre effects).

- 1. **Secondary study parameter(s)**

Secondary endpoints will be analysed in an exploratory manner at a two-sided significance level of 5%. Safety and tolerability parameters will be analysed descriptively.

Analysis of time-dependent probabilities of critical events will be performed using the Kaplan-Meier method. Furthermore, multivariate event analyses will be performed using Cox proportional hazard regression models. In addition, for the purpose of a supportive sensitivity analysis, multiple imputation procedures will be applied.

COST-EFFECTIVENESS ANALYSIS

The cost-effectiveness analysis will be performed alongside the proposed clinical trial to assess the cost- effectiveness of FOR versus ACDF. There will be two separate outcome measures for the cost- effectiveness analysis, resulting in two incremental cost-effectiveness ratios (ICERs) for FOR as compared to ACDF, the first is incremental costs per extra percentage of patients with arm pain relief, the second is incremental costs per Quality Adjusted Life Year (QALY) gained. The analysis will be performed taking a societal perspective. The time horizon will be equivalent to the full follow-up of the clinical study, which is 24 months. According to pharmaco-economic guidelines (6) discounting will be applied for costs (4%) and effects (1.5%) in the second year. A number of sensitivity analyses will be performed to identify the impact of variables such as the costs of the FOR and ACDF procedures, resource use, and effect size, on cost-effectiveness. A cost-effectiveness acceptability curve will be constructed, based on bootstrap simulations, showing the probability of FOR being cost-effective compared to ACDF at varying levels of the willingness to pay, for either one additional percentage of patients with arm pain relief, or one additional QALY.

PATIENT OUTCOME ANALYSIS

The first outcome for the cost-effectiveness analysis is the percentage of patients with arm pain relief, which will be measured and analysed by the VAS, Odom's criteria, neurological testing and the NDI for the extent of neck pain. The second outcome is QALYs, which are assessed by means of the EQ-5D questionnaire (11) EQ-5D scores will be converted into health state utilities, ranging between 0 and 1, with a higher utility indicating a better health-related Quality of Life (QoL). These utilities will be multiplied with follow-up time spent in that particular health state (area under the curve) to eventually convert into QALYs.

BUDGET IMPACT ANALYSIS (BIA)

Based on the results of the clinical study and the cost-effectiveness analysis, a budget impact analysis will be performed to inform decision makers on the financial consequences of implementing FOR as treatment of first choice for cervical soft disc/osteophytic disease in the Dutch health care system. The BIA will be performed according to the principles of the ISPOR task force (7) and from both the perspective of the government (societal and BKZ – budgettair kader zorg) as well as a third party payer/healthcare insurers perspective. The trial results will be extrapolated, by means of a simple model, from a time horizon of 24 months to 5 years, and for the entire Dutch population concerned. The extrapolation will assume a constant incidence of cervical soft disc /osteophytic disease. Also, we expect that the proportion of cases eligible for surgical intervention will be stable over time. Therefore the extrapolation will be linear. Sensitivity analyses will be performed on relevant parameters such as the eventual substitution rate of FOR versus ACDF (may not be 100%), the uptake of FOR with time, costs of the procedures and other cost items. We will assume that current usual care already consists of a mix of ACDF and FOR, i.e. 90% and 10%, respectively.

1. **ETHICAL CONSIDERATIONS**
   1. **Regulation statement**

It is the responsibility of the investigator that this study will be conducted in accordance with the Declaration of Helsinki and in compliance with the Medical Research Involving Human Subjects Act (WMO).

- 1. **Recruitment and consent**

Patients will be informed in person (by the neurosurgeon and they will receive the written information concerning this trial. They will be informed about the procedure in this study, the duration and possible risks. Patients are allowed to take one week to make the decision whether they will take part in this study. The patient will be required to sign the written informed consent form if he wants to take part in this study. The right to the participant to refuse to participate without giving reasons will be respected. All participants are free to withdraw at any time from the protocol without giving reasons and without prejudicing further treatment.

- 1. **Benefits and risks assessment, group relatedness**

As described in chapter 5, the procedure is part of standard care for many years in most hospitals. It was shown that the risk of complications due to the procedure in both techniques are equal and due to the risk of the operation itself and is not due to the study procedures. The surgical procedure itself does not appreciably increase the risk of serious adverse events beyond the risk of undergoing the surgical procedure. Therefore we can conclude that the FACET study is a low to moderate risk study (according to the NFU risk classification) in which the benefits are high. In total 80-90 % of the patients are relieved of their cervico brachialgia after surgery.

- 1. **Compensation for injury**

The sponsor/investigator has a liability insurance which is in accordance with article 7 of the WMO. The sponsor (also) has an insurance which is in accordance with the legal requirements in the Netherlands (Article 7 WMO). This insurance provides cover for damage to research subjects through injury or death caused by the study.

The insurance applies to the damage that becomes apparent during the study or within 4 years after the end of the study.

1. **ADMINISTRATIVE ASPECTS, MONITORING AND PUBLICATION**
   1. **Handling and storage of data and documents**

The investigator will permit access to all patient source documents including original medical records by applicable regulatory authorities or the Medical Ethics Committee (METc), and consent to this documentation being available for review on request. The CRF will be completed for every patient and will capture all relevant patient information including details of any complications or adverse events. The CRF will be completed by properly trained and authorized personnel and each CRF will be approved by the investigator ensuring the data accurately reflects the patients’ clinical condition. The clinical data in the CRF will be entered into a computerized database for secure storage and in preparation for analysis.

Data will be handled confidentially. Where it is necessary to be able to trace data to an individual subject, a subject identification list is used to link the data to the subject. This code will not be based on the patient initials and birth-date, but will be based on the study site followed by the number of entering in the study (for example, the first patient included in the UMCG get number 10-001). The key to the code will be safeguarded by the investigator at the participating sites. The handling of personal data will comply with the Dutch Personal Data Protection Act (Wbp).

- 1. **Monitoring and Quality Assurance**

Monitoring activities will be performed on the basis of the Monitoring Plan. We will arrange 1 investigator meeting before actual start of the study and 2 or 3 monitor visits per site depending on the inclusion rate and findings of the monitor ( in total 15 monitor visits) will be performed. Monitoring will be performed in compliance with Good Clinical Practice and applicable national regulations.

No initiation visits (per site) will be performed. Instead, one investigator meeting in the Centre of The Netherlands will be organized. Monitoring objectives, tasks and issues will be presented by the study coordination institute (TCC).

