**Main study parameters/endpoints:**

Primary outcome measure will be self-reported brachialgia by the Visual Analoge Scale/Odom’s criteria (4 point Likert scale for self-reported brachialgia). The secondary outcomes include Work Ability (Work Ability Index, single item), Quality of Life (EQ-5D), Neck Pain (VAS), Neck disability index (NDI), Complications and Productivity related costs (iPCQ) and medical costs (iMCQ).

**Nature and extent of the burden and risks associated with participation, benefit and group relatedness:** Patients are treated within the concept of “care as usual”. Both operative techniques are part of the neurosurgeons basic skills and training. Both operative techniques are indicated techniques to operate on cervical discal herniations. However, as differences in risks and clinical outcome between both procedures have never been studied in a comparative setting, their exact magnitude and nature is not yet known and therefore their assessment is one of the objectives of the study.

The burden for patients participating in this trial is low. Patients are asked to fill out questionnaires at baseline and after 6, 26, 52, 78 and 104 weeks. Time to fill out the questionnaires is approximately 30 minutes per follow up moment. There are no benefits compared to care as usual.

1. **INTRODUCTION AND RATIONALE**

Cervical radiculopathy is a disease with a significant impact on the patient’s quality of life. Most patients with a cervical radiculopathy belong to the labour force. Therefore temporary disability due to the radiculopathy often leads to health care problems and loss of productivity.

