The presented studies of clinical effectiveness demonstrate a similar effect on relief of arm pain, but a lower chance of serious complications needing longer hospital stay or readmission. We assume a 10% difference between the ACDF and FOR, which means that serious complications would occur in 10% more of the cases in the ACDF, and 2 weeks extra hospital care attributed to a serious complication (10 work days). We also assume that of the 1300 patients treated per year, 50% will be among the working population, in a 75% part-time job on average. The standard mean costs of a working day in the Netherlands is €230 (11). Thus: 650 working patients x 10% with serious complications x 7.5 workdays lost per patient = 487.5 work days saved with the FOR procedure. This amounts to a total of €112.125.

1. **OBJECTIVES**

Primary Objective:

Is the posterior cervical foraminotomy (FOR) technique effective in comparison to the anterior cervical discectomy with fusion (ACDF) with regards to reduction of cervical radicular pain measured by the ODOM criteria (4 point Likert scale) and VAS arm pain.

Secondary Objective(s):

- 1. Does the FOR operation lead to faster return to work, after operation, in comparison with the ACDF technique,
  2. Does the FOR operation lead to a higher quality of life in comparison with the ACDF technique,
  3. Does the FOR operation lead to more or less neck disability and/or more or less postoperative neck pain in comparison with the ACDF technique,
  4. Does the FOR operation lead to less or more complications in comparison with the ACDF technique,
  5. Does the FOR operation lead to lower productivity losses and medical costs in comparison with the ACDF technique.
  6. What would be the budget impact of implementing the FOR technique, if it were to replace the ACDF technique as the recommended strategy for patients with a CRS due to soft disc compression or osteophyte compression of a cervical root

1. **STUDY DESIGN**

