**Table 3. Cost differentiation with number of patients reporting costs**

|  | **Posterior Surgery**  **n=119** | **Anterior Surgery**  **n=124** | **Difference (95% CI)** |
| --- | --- | --- | --- |
| General practitioner | 634 | 613 | 28 |
| *n reported* | 71 | 78 |  |
| Physiotherapist  *n reported* | 1,179  50 | 1,450  55 | -355 |
| Company doctor | 158 | 182 | -31 |
| *n reported* | 47 | 41 |  |
| Other primary care^b^  *n reported* | 693  30 | 804  28 | -146 |
| Care at home^c^  *n reported* | 886  0 | 1,450  6 | -739 |
| Neurosurgeon  *n reported* | 338  85 | 298  78 | 52 |
| Other outpatient clinic visits  *n reported* | 734  49 | 1,062  47 | -430 |
| Pain medication  *n reported* | 231  51 | 273  49 | -55 |
| Emergency department^d^  *n reported* | 505  15 | 815  15 | -406 |
| Hospital admissions  *n reported* | 1,612  18 | 2,437  24 | -1,082 |
| Additional health care costs^e^  *n reported* | 1,693  40 | 1,991  45 | -391 |
| **Total health care costs** | **12,248** | **16,055** | **-3,807 (-6,580 to -1,127)** |
|  |  |  |  |
| Absenteeism paid work^f^  *n reported* | 8,708  43 | 8,818  40 | -110 |
| Presenteeism paid work^f^  *n reported* | 2,434  25 | 560  18 | 1,874 |
| Absenteeism unpaid work^f^  *n reported* | 4,655  64 | 4,653  53 | 2 |
| **Total productivity losses**  **Total societal costs** | **15,797**  **28,046** | **14,031**  **30,086** | **1,767 (-5,358 to 8,373)**  **-2,674 (-19,603 to 5,547)** |

*Abbreviations: Confidence Interval (CI), Standard deviation (SD), number (n)*

*Values are presented as pooled estimated means in rounded Euros. ‘N reported’ are the number of patients that reported costs for a certain subcategory in the original data set.

^a^ Surgical costs include the price for the procedure, implants and haemostatics, and costs for days of admission to the hospital for the initial intervention.

^b^ Other primary care includes visits to social workers, occupational therapists, speech therapists, dieticians, alternative therapists and psychologists.

^c^ Care at home was not reported by any of the patients in the posterior group, to note is that the reported costs are estimated pooled means, using multiple imputation and bootstrapping.

^d^ Emergency department includes visits to the emergency department and transportation to the hospital by ambulance.

^e^ Additional health care costs include day-care or admissions to a health institution other than a hospital, rehabilitation centre or psychiatric institution.

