^f^ Absenteeism is the amount of days that a patient was absent from work times the Dutch reference wage per day. The ‘friction cost method’ was applied, assuming that after a period of 85 days of complete absence, an employee gets replaced by another worker, and productivity would be restored. Presenteeism is the loss of productivity by patients that were not able to fully fulfil their jobs. It was calculated by the proportion of productivity loss of a general working day, times the duration in days, times the average wage per day. Unpaid work is the loss of productivity during unpaid activities such as household work and volunteering. It was calculated by hours a day, times the duration in days, times the Dutch reference price for one hour of unpaid work.

**
[figure not shown]
Figure 1.** **Incremental Cost-Effectiveness Plane comparing Cost Difference and Neck Disability Index from a Societal Perspective.**

*Abbreviations: Multiple imputation sets (MI).*

Figure 1 depicts the cost difference of posterior versus anterior surgery on the vertical axis in Euros, and the difference in Neck Disability Index (NDI) score between groups on the horizontal axis.

**
[figure not shown]
Figure 2. Incremental Cost-Effectiveness Plane comparing Cost Difference and Neck Disability Index from a Healthcare Perspective.**

*Abbreviations: Multiple imputation sets (MI).*

Figure 2 depicts the cost difference of posterior versus anterior surgery on the vertical axis in Euros, and the difference in Neck Disability Index (NDI) score between groups on the horizontal axis.

**
[figure not shown]
Figure 3. Incremental Cost-Effectiveness Plane comparing Cost Difference and Odom Criteria from a Societal Perspective.**

Figure 3 depicts the cost difference of posterior versus anterior surgery on the vertical axis in Euros, and the difference in proportion of Successful Odom Scores between groups on the horizontal axis. A successful Odom score is the proportion of patients graded ‘excellent’ or ‘good’ on the modified Odom criteria, based on patients with complete cost data for all time points and an available Odom score (n=80 in the posterior group and n=73 in the anterior group).

**
[figure not shown]
Figure 4. Incremental Cost-Effectiveness Plane comparing Cost Difference and Odom Criteria from a Healthcare Perspective.**

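### The protocol's cost list names absence from work, while Supplementary Table 3 also counts presenteeism, and that one item decides the direction of the productivity estimate

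*Combined protocol and SAP*

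**What the plan says.** The protocol itemises costs in one place, section 6.3 (Study procedures), under Costs. The list runs through the operation, hospital care, medication for the diagnosis and outpatient visits, and closes with "GP visits, home care, and productivity costs due to absence from work". The sources follow in brackets, "Productivity Costs Questionnaire iPCQ, Medical Consumption Questionnaire iMCQ", without saying which iPCQ items are to be valued.

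Other sections are worded differently. Secondary objective 5 asks: "Does the FOR operation lead to lower productivity losses and medical costs in comparison with the ACDF technique". The Summary gives productivity-related costs from the iPCQ as a secondary outcome. The cost-effectiveness section states: "The analysis will be performed taking a societal perspective". By contrast, the Summary objective, the efficiency rationale in the Introduction and the hypothesis under Study design refer to work absenteeism. None of these sections names presenteeism.

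Supplementary Table 3 builds its productivity total from three rows: absence from paid work, presenteeism in paid work, and absence from unpaid work. Its footnote f explains the last two: "Presenteeism is the loss of productivity by patients that were not able to fully fulfil their jobs", and "Unpaid work is the loss of productivity during unpaid activities such as household work and volunteering".

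**The concern.** Presenteeism is output lost while the patient is at work. It is not absence, so it does not fit the item on the section 6.3 list, although it does fit the broader wording of objective 5. The productivity and societal cost endpoints can therefore be read in two ways, and the documents do not say which reading was planned.

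The choice matters because presenteeism carries nearly all of the productivity contrast in Table 3. It enters the point estimate for objective 5, the two planned societal incremental cost-effectiveness ratios (cost per extra percentage of patients with arm pain relief, and cost per QALY), and the acceptability curve drawn from bootstrap replicates. These are shifted by the choice of components whether or not the difference is statistically significant.

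**Working it through.** All inputs are from Supplementary Table 3, in euro (posterior n=119, anterior n=124). Differences are posterior minus anterior.

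| Row | Posterior | Anterior | By subtraction | Printed |
|---|---|---|---|---|
| Absence, paid work | 8,708 | 8,818 | -110 | -110 |
| Presenteeism | 2,434 | 560 | +1,874 | 1,874 |
| Absence, unpaid work | 4,655 | 4,653 | +2 | 2 |
| Productivity total | 15,797 | 14,031 | +1,766 | 1,767 (-5,358 to 8,373) |
| Health care total | 12,248 | 16,055 | -3,807 | -3,807 (-6,580 to -1,127) |
| Societal total | 28,046 | 30,086 | -2,040 | -2,674 (-19,603 to 5,547) |

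**1. Reproducing the table.**
- Productivity: 8,708 + 2,434 + 4,655 = 15,797 and 8,818 + 560 + 4,653 = 14,031. Both match, and the difference matches to within 1 euro of rounding.
- Societal arm totals: 12,248 + 15,797 = 28,045 (printed 28,046) and 16,055 + 14,031 = 30,086. Both match to within rounding.
- Societal difference: 28,046 - 30,086 = -2,040, and -3,807 + 1,767 = -2,040. The printed -2,674 does not reproduce by either route.

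**2. Productivity difference by component set.**
- Paid absence alone: -110.
- Paid and unpaid absence: -110 + 2 = -108.
- All three rows: -110 + 1,874 + 2 = +1,766 (printed 1,767).

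The sign changes when presenteeism is added. How unpaid work is classed makes a difference of 2 euro.

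**3. Societal difference.**
- Paid absence alone: 12,248 + 8,708 = 20,956 and 16,055 + 8,818 = 24,873, so 20,956 - 24,873 = -3,917.
- Against -2,040: 1 - 2,040/3,917 = 0.479, a saving 48% smaller.
- Against the printed -2,674: 1 - 2,674/3,917 = 0.317, a saving 32% smaller.
- Starting from paid plus unpaid absence (-3,915) leaves both percentages unchanged after rounding.

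**4. The mismatch in the societal row.** -2,674 / -2,040 = 1.31. The health care component rows show much the same ratio of printed to subtracted difference, for example physiotherapist -355 against 1,179 - 1,450 = -271, and hospital admissions -1,082 against 1,612 - 2,437 = -825. The health care total and the productivity rows do not. The documents do not say how the difference column was obtained.

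**5. Precision.** Presenteeism costs were reported by 25 posterior and 18 anterior patients. The table gives no interval for single rows, so an interval for the total without presenteeism cannot be derived from the documents.

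**The case against.** The list in section 6.3 neither excludes presenteeism nor says that it is exhaustive. It names the iPCQ without restricting its items, and objective 5, the Summary outcome and the societal perspective all allow a wider reading. On this view the fault is loose wording in one procedures paragraph. Part of that stands: the protocol is ambiguous, and it cannot be said to limit productivity costs to absence. But the broader sections give a goal, an instrument and a perspective. Section 6.3 alone itemises what is costed, and its wording fits the absenteeism language elsewhere.

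The difference of -110 is about 1% of the cost in each arm, and the productivity interval runs from -5,358 to 8,373. A change of sign around zero can be noise. That stands too, and limits the point to estimates and how they are presented.

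Table 3 prints every component with the number of patients reporting, and baseline Table 2 has the same productivity rows. A reader can redo the sums, but not the intervals, ratios or acceptability curve.

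Some stronger readings are tempting and are not supported:
- **Favourable selection of components.** Adding presenteeism reduces the saving with foraminotomy, against the protocol's own hypothesis of lower costs. The protocol is labelled as the original; an amendment or economic analysis plan may exist that is not in these documents.
- **The list as exhaustive for health care too**, so that the physiotherapist, company doctor, other primary care and additional care rows should also come out. The text does not say so, and the size of such a change is unclear: those four rows differ by -271 - 24 - 111 - 298 = -704 by subtraction but by -355 - 31 - 146 - 391 = -923 as printed.
- **Absence alone as the right societal measure.** It is the less complete one. The choice of main definition is a trade-off.

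**Conclusion.** The point holds as an unreconciled definition with a visible effect on the estimates. Presenteeism, which the protocol's cost list does not name, takes the productivity difference from -110 (or -108) to +1,767 euro. The societal saving becomes 48% smaller if the arm totals are right and 32% smaller if the printed difference is right. A reader might infer that it is nearly halved, but that rests on -2,040, which the table does not print; both figures have to be given until the row is checked. The agreement of two routes on -2,040 makes -2,674 the figure in doubt.

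A reader might also infer that foraminotomy raises productivity costs, or that it lowers them. Neither is established, because the productivity and societal intervals both include 0.

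This rests on the Table 3 arm means as printed, on totals being sums of their rows (confirmed for the productivity and societal totals), and on no intermediate plan having redefined the components. It concerns a secondary, economic endpoint and does not touch the primary clinical comparison.

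**What to change.** - State one set of productivity components and use it in both section 6.3 and Table 3. Either set can be the main one, provided that the choice is explicit.
- Whichever is main, report the productivity total, the societal total, both societal cost-effectiveness ratios and the acceptability curve with and without presenteeism, with bootstrap confidence intervals.
- Label presenteeism as an item that is not on the protocol's cost list, and state that the direction of the productivity point estimate depends on it and is not established.
- Correct the printed societal difference of -2,674, or explain why it departs from -2,040. Check the health care component rows, which show the same ratio of about 1.3, at the same time.

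No new data are needed. The rows have already been computed, so the work is a re-sum, one more bootstrap run and a sentence in section 6.3. The downside is one extra set of results to present. The planned sensitivity analyses on resource use give a natural place for it.
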